### Sample size

Sample size is calculated based on migraine, biofeedback training [29] and aerobic training articles [30]. Using g power statistical tool F test, ANOVA: repeated measure, between factors, and with 0.4 effect size, 0.05 alpha error, 0.95 beta error, 3 groups, 4 outcome measurements the sample size is 66. Then, further adjustment of sample size to accommodate 25% dropout rate [31] gives the final estimated value to 88.

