### Study goal and objective

If an earlier, migraine is left untreated or undiagnosed, it is reported that around 2.5% of individuals with migraine are considered to have a chronic condition, defined as presenting with more than 15 headache days within a month. Subclassifications of the disease (migraine with and without aura and chronic migraine) occur clinically at various severity levels and coexist with numerous comorbidities. For this reason, several studies encourage a multidisciplinary and tailored treatment approach for these patients [26,27]. This preliminary randomized control trial aims to analyse the effectiveness of aerobic training among university students with migraine symptoms. The main objective is to determine the preliminary effect of aerobic training on migraine pain level, sleep quality, quality of life, and resting-state brain waves compared with EMG biofeedback training and placebo.

The alternative hypothesis of this study will be the aerobic training will be superior to EMG biofeedback training and placebo group in improving migraine pain level, sleep quality, quality of life, and resting-state brain waves. The null hypothesis will be the aerobic training is same as to EMG biofeedback training and placebo group in improving migraine pain level, sleep quality, quality of life, and resting-state brain waves. Although the Migraine Research Foundation listed three main types of non-drug treatments for migraine: lifestyle advice, therapies, and exercises. Some common aerobic exercises such as walking, jogging, a behavioral weight loss program, cycling, and a combination of cross-training, walking, jogging, and cycling are suggested to be beneficial to migraine patients but there remains no specific protocol established till now. Hence, this study will contribute to the research field by establishing an aerobic training protocol for patients with migraine symptoms.

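### The 0.95 in the sample-size statement is the power of a three-group omnibus F test, not a beta error and not the power to show aerobic training superior to both comparators

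*Protocol article*

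**What the plan says.** The Sample size section of the protocol article names the routine, an F test, and its inputs: "ANOVA: repeated measure, between factors, and with 0.4 effect size, 0.05 alpha error, 0.95 beta error, 3 groups, 4 outcome measurements". The result is 66, raised to 88 for 25% dropout. The section states no correlation between measurements, no allocation ratio, no pattern of group means and no pairwise difference.

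The Study goal and objective section states the alternative hypothesis that "the aerobic training will be superior to EMG biofeedback training and placebo group in improving migraine pain level", and it goes on to list sleep quality, quality of life and resting-state brain waves. The null is that aerobic training is the same as the two comparators.

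The Methodology section and the Procedure and stages section schedule outcome assessment twice, at baseline and at week 6. Resting-state EEG is the primary endpoint. The Statistical analyses section names a mixed design analysis and no pairwise contrast.

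**The concern.** Two things in the sizing sentence do not fit. First, a beta error of 0.95 would mean 5% power, which nobody would plan for. Second, a between-groups F test on three arms has 2 numerator degrees of freedom and rejects when any of the arms differ. The hypothesis needs two specific wins: aerobic over biofeedback and aerobic over placebo. The printed power therefore answers a different question from the printed hypothesis.

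The exposed contrast is aerobic training against an active comparator, which the Background itself presents as beneficial. Readers who are told that the trial has 0.95 power may give a non-significant aerobic-versus-biofeedback result more weight than it can bear, particularly beside a null worded as sameness.

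**Working it through.** **Inputs.** From the Sample size section: f = 0.4 (effect size of this F-test routine), alpha 0.05, k = 3 groups, m = 4 measurements, N = 66, dropout 25%. Assumed because not stated: correlation rho = 0.5, equal groups (66/3 = 22 each), and two-sided 0.05 per contrast with no multiplicity adjustment.

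**1. Reproduce 66 and 88.** For the between factor, lambda = f² × N × m / (1 + (m − 1) × rho), with df 2 and N − 3.

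- N = 66: lambda = 0.16 × 66 × 4 / 2.5 = 16.90, power 0.958.
- N = 63: lambda = 0.16 × 63 × 4 / 2.5 = 16.13, power 0.949.

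So 66 is the smallest multiple of 3 that reaches 0.95, and 66 / 0.75 = 88. The 0.95 is power; beta is 0.05. The correlation matters: with m = 4 the required N is 30, 51, 78 or 87 at rho = 0, 0.3, 0.7 or 0.8. The pair m = 2, rho = 0.3 also returns 66.

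**2. Does omnibus power carry over to the hypothesis?** Suppose aerobic equals biofeedback and both beat placebo, scaled to f = 0.4. Lambda depends only on f, so omnibus power is still 0.958. The hypothesis is false in this case, and the chance of declaring aerobic superior to both is about 0.025.

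**3. Power when aerobic truly beats both.** Scale the means so that their standard deviation across arms is 0.4.

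- Biofeedback = placebo: pattern (1, 0, 0) has SD √(2/9) = 0.471, so both differences are 0.4 / 0.471 = 0.85 SD.
- Equally spaced: pattern (1, 0, −1) has SD √(2/3) = 0.816, so the differences are 0.4 / 0.816 = 0.49 SD against biofeedback and 0.98 SD against placebo.

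The variance of a participant's mean is (1 + (m − 1) × rho) / m, which is 0.625 for m = 4 and 0.75 for m = 2 at rho = 0.5. Simulation of two t tests that share the aerobic arm (pooled variance, 63 df, 22 per group) gives:

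| m, rho | Omnibus | Both, biofeedback = placebo | Both, equally spaced |
|---|---|---|---|
| 4, 0.5 | 0.958 | 0.89 | 0.52 |
| 2, 0.5 | 0.92 | 0.82 | 0.45 |
| 4, 0.3 | 0.99 | 0.96 | 0.64 |
| 4, 0.7 | 0.91 | 0.81 | 0.44 |

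With one-sided 0.05 per contrast at m = 4 and rho = 0.5, the two patterns give 0.946 and 0.65.

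**4. Where the loss lies.** In the equally spaced case at m = 4 and rho = 0.5, aerobic versus placebo alone has power 0.98 and aerobic versus biofeedback 0.52. Nearly all of the shortfall comes from the active comparator.

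**The case against.** The trial calls itself a pilot of preliminary efficacy, sizing a three-arm trial on the omnibus test is common, and pairwise contrasts are often left to an analysis plan that is not shown here. That lowers the weight. It does not remove the mismatch, because the article itself prints both a superiority hypothesis against two comparators and a figure of 0.95.

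The size of the shortfall depends on assumptions that the article does not supply. That objection stands. Correlation, sidedness and mean pattern are all open, so only a range is defensible. A reader might infer that power always falls at least 6 points short of 0.95, but one-sided testing in the favourable pattern gives 0.946 and a correlation of 0.3 gives 0.96. Nor should an arbitrarily low figure be quoted: moving biofeedback closer to aerobic training can make power as small as one likes.

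The four-measurement figures should also not simply be printed as the trial's power, since only two assessments are scheduled. The four may be a count of the outcomes. That also stands, and it is why the m = 2 row is shown.

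Finally, these figures concern one outcome, while the hypothesis lists four. They are not the power of the whole hypothesis.

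**Conclusion.** The point holds. The 0.95 is mislabelled as beta, and it is the power of the omnibus test only. For showing aerobic training superior to both comparators on a single outcome, with 22 completers per group, two-sided 0.05 per contrast and correlation 0.5, power is about 0.52 to 0.89 with four measurements and about 0.45 to 0.82 with two. The lower end is for equally spaced means and the upper end for biofeedback no better than placebo. In every case calculated it lies below the omnibus power under the same assumptions.

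Three stronger readings are not supported. The sample-size arithmetic is not wrong: 66 and 88 both reproduce. The trial was not planned with 5% power. And nothing in the article says that a non-significant contrast will be read as equality; that is a risk of the wording, not a stated plan.

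**What to change.** Keep 88 and revise the Sample size section as follows.

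- Label 0.95 as the power (beta 0.05) of the three-group omnibus F test.
- Reconcile the four measurements with the two scheduled assessments, state the correlation used, and restate the omnibus power accordingly (0.92 at two measurements and correlation 0.5).
- State the power for aerobic versus biofeedback and aerobic versus placebo on the primary outcome as a range, giving the assumed correlation, sidedness and pattern of means.
- Say that the aerobic-versus-biofeedback contrast will be reported with its confidence interval, and that non-significance will not be read as equality.

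The cost is a reworded paragraph and a less favourable stated power. No participants or procedures are added.

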## Methodology

This study is a pilot randomized control trial with a pre-and post-test design that focuses on the preliminary efficacy of aerobic training among university students with migraine symptoms. The primary endpoint is resting-state electroencephalography (EEG). The secondary endpoints are sleep quality, quality of life, and migraine pain level. This study will be conducted at Physiotherapy Center, Universiti Tunku Abdul Rahman, Sungai Long Campus. The outcome measures will be performed at baseline and end of intervention (6^th^ week) to compare the data obtained. The study is approved by UTAR Scientific and Ethical Review Committee (U/SERC/188/2022). The informed consent form will be signed and dated before the start of the actual intervention. Parallel assignment intervention model will be used. The study is also registered with ClinicalTrials.gov Protocol Registration and Results System (Identifier: NCT05741775).

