### Statistical analyses

The planned statistical analysis for each phase: Data collected will be computed and analyzed using IBM Statistical Package for Social Science (SPSS) version 22.0 to produce the study results. Descriptive analyses using the mean and the standard deviation will be used to examine the data obtained. Descriptive statistics will be used to analyse the demographic data of every subject at their baseline. A box plot graph will be used to portray the distribution of data for example age, gender, year of study, area of study, and physical activity level.

The distribution of data will be analysed using normality of distribution. Mixed design analysis and intention-to-treat analysis will be used to assess the efficacy of aerobic training.

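### The sample size enters 4 repeated measurements where each outcome is measured at two visits, and sizes a group effect that averages in baseline, so the stated 0.95 power is not established for this design

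*Protocol article*

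**What the plan says.** The Sample size section of the protocol article describes the calculation as follows: "Using g power statistical tool F test, ANOVA: repeated measure, between factors, and with 0.4 effect size". The remaining inputs and the result are "0.05 alpha error, 0.95 beta error, 3 groups, 4 outcome measurements the sample size is 66". A 25% dropout allowance then raises 66 to 88. No correlation among repeated measurements is given.

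The Methodology section describes a pre-test/post-test design: "The outcome measures will be performed at baseline and end of intervention", the latter being week 6. Procedure and stages repeats these two assessments and adds no other. The Outcomes section lists four different outcomes: resting-state EEG (primary), and sleep quality, quality of life and migraine pain level (secondary).

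On the analysis, the Statistical analyses section says: "Mixed design analysis and intention-to-treat analysis will be used to assess the efficacy of aerobic training". It does not name the term of the mixed design that decides efficacy.

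**The concern.** Three things in the sample size paragraph do not fit the trial described elsewhere in the article.

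- **Number of measurements.** In a repeated-measures power routine this input is the number of times one variable is measured on each participant. Averaging more repeats reduces the error, so a larger entry gives a smaller required sample. The trial has two occasions, not four. Four outcomes on different scales are not repeats of one variable and cannot be averaged.
- **Effect tested.** The option "ANOVA: repeated measure, between factors" tests group means averaged over all occasions. In a pre/post trial one of the two occasions is baseline, where randomised groups differ only by chance. The treatment effect lies in the group-by-time term or in a baseline-adjusted comparison at week 6.
- **Label.** "0.95 beta error" would literally mean 5% power.

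This is the only operating characteristic that the article states. Although the trial is called a pilot, it sets a superiority hypothesis and justifies its size by formal power. A null result would therefore be read against a 95% power that has not been shown for this design.

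**Working it through.** **Inputs.** From the Sample size section: effect size f = 0.4, so f² = 0.16; alpha 0.05; k = 3 groups; m = 4 measurements; 0.95, read as power; dropout 25%. From Methodology: two occasions. Assumed: correlation ρ = 0.5 between measurements, with 0.3 to 0.7 as the range.

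**Step 1. Reproduce the stated figure.** For the between-factors test, λ = f² × N × m / (1 + (m − 1)ρ), with a noncentral F on k − 1 and N − k degrees of freedom and N in multiples of 3.
- N = 66, m = 4, ρ = 0.5: λ = 0.16 × 66 × 4 / 2.5 = 16.90, power 0.958.
- N = 63: λ = 16.13, power 0.949.

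So 66 is the smallest N reaching 0.95, and 66 / 0.75 = 88. With m = 4, ρ = 0.3 would have given 51 and ρ = 0.7 would have given 78. Reading 0.95 as power is what returns 66; at 5% power the smallest N tried (6) already suffices.

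**Step 2. Same test with the two actual occasions.** λ = 0.16 × N × 2 / (1 + ρ).

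| ρ | λ at N = 66 | Power at 66 | N for 0.95 |
|---|---|---|---|
| 0.3 | 16.25 | 0.951 | 66 |
| 0.5 | 14.08 | 0.917 | 78 |
| 0.7 | 12.42 | 0.879 | 87 |

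At ρ = 0.5, 78 completers correspond to 78 / 0.75 = 104 enrolled.

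**Step 3. Which effect is tested.** Suppose the groups are equal at baseline and separated by f = 0.4 at week 6. The formulas become:
- Between-factors main effect: averaging with a null baseline halves f to 0.2, so λ = N f² / (2(1 + ρ)).
- Group-by-time (change): λ = N f² / (2(1 − ρ)).
- Week-6 comparison adjusted for baseline: λ = N f² / (1 − ρ²), with one further degree of freedom lost to the covariate.

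With N f² = 66 × 0.16 = 10.56, at ρ = 0.5:
- main effect: λ = 10.56 / 3 = 3.52
- group-by-time: λ = 10.56 / 1 = 10.56
- baseline-adjusted: λ = 10.56 / 0.75 = 14.08

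| Test, 66 completers | ρ = 0.3 | ρ = 0.5 | ρ = 0.7 |
|---|---|---|---|
| Between-factors main effect | 0.40 | 0.36 | 0.32 |
| Group-by-time | 0.67 | 0.82 | 0.97 (0.965) |
| Baseline-adjusted week 6 | 0.85 | 0.92 | 0.98 |

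The 0.92 in Step 2 and the 0.92 for the baseline-adjusted test coincide because (1 + ρ)/2 and 1 − ρ² both equal 0.75 at ρ = 0.5. They are different tests under different assumptions about f.

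**The case against.** Much of the opposing case concerns how far the conclusion can be pushed, and several parts of it stand.

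- **The correlation is assumed.** Two occasions with a correlation of 0.25 to 0.30 also give exactly 66 at 0.95 power. A reader might infer that 66 can arise only from four measurements; that is true at correlation 0.5 and not in general. It does not rescue the text, which prints 4, and four measurements at correlation 0.3 would give 51.
- **The power may exceed 0.95.** The baseline-adjusted comparison reaches 0.953 at correlation 0.6 and 0.984 at 0.7, and group-by-time reaches 0.965 at 0.7. So a reader cannot conclude that the trial falls short of 0.95, only that 0.95 has not been shown.
- **The 0.36 is a scenario.** It requires that f = 0.4 is a week-6 separation only and that the group main effect is the efficacy test. The article says neither, and the planned mixed design contains a group-by-time term. It would be wrong to quote 0.36 as this trial's power.
- **What the 4 counts is an inference.** The EEG is recorded with eyes open and with eyes closed, so two conditions at two visits would also make four, and the headset has four sensors. The word used is outcome measurements and there are exactly four outcomes, so that reading is the most natural. None of these readings removes the averaging-in of baseline.
- **Intention-to-treat.** If all 88 were analysed, Step 2 at correlation 0.5 gives 0.975. This is an upper bound, because the plan itself expects 66 evaluable participants.
- **Pilot status and arithmetic.** The shortfall from the number of occasions alone is moderate, and the arithmetic, including the dropout step, is correct. The fault lies in the inputs and the choice of test.

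**Conclusion.** The calculation is wrong as written. It enters four measurements for a trial with two assessments, tests an effect that dilutes any treatment difference with baseline, and calls power a beta error. At an assumed correlation of 0.5, correcting the occasions alone lowers power from 0.958 to 0.917 at 66 completers. For the tests that carry the treatment effect in this design, power at a week-6 separation of f = 0.4 is about 0.82 (group-by-time) or about 0.92 (baseline-adjusted), with ranges that include 0.95 at the higher correlations. The supported conclusion is that the unconditional 0.95 is not established for this design; the documents do not support saying that the trial is necessarily underpowered. All figures rest on the assumed correlation of 0.3 to 0.7 and on 66 completers; the 0.82 and 0.92 also assume that f = 0.4 is the week-6 separation.

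**What to change.** Keep 66 completers and 88 enrolled, and change the text as follows.

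1. In Sample size, replace the four outcome measurements by two occasions, and describe 0.95 as power wherever it is kept as an input.
2. State the assumed correlation between baseline and week 6, and say that f = 0.4 refers to the week-6 separation, if that is what is meant.
3. Name the same decisive comparison in Sample size and in Statistical analyses: either the baseline-adjusted week-6 group comparison or the group-by-time term of the mixed design. Changing only the sample size paragraph would leave a new mismatch with the analysis section.
4. Replace the unconditional 0.95 by the power of that comparison: about 0.92 (0.85–0.98 for correlation 0.3–0.7) if baseline-adjusted, or about 0.82 (0.67–0.97) if group-by-time.

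The cost is a less favourable stated power and a wording change in the analysis section. No participants or visits are added.

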### Randomization

A simple random sampling method will be employed as the sampling technique in recruiting the subjects. Upon successful recruitment of participants, and with Migraine Disability Assessment Scale (MIDAS) Questionnaire, the subjects will be allocated into either of the three groups (Group 1: aerobic training, Group 2: biofeedback training, Group 3: placebo group). The subjects will be given a random number in an excel sheet and ranked. Following ranking, the ranked participant will be divided by size and group accordingly.

Simultaneously using MIDAS, each group will have 7–10 participants depending on each level of disability on MIDAS. In the Migraine Disability Assessment Scale (MIDAS) Questionnaire that assesses headache-related disability, the respondents are required to answer five questions. The number of days in each question will be summed up and the scoring indicates the activity limitation due to migraine in the past 3 months. The participants are then categorized into no or little disability (0–5), mild disability (6–10), moderate disability (11–20), and severe disability (21+) (Stewart et al., 2001).

### Blinding

A single blinding method will be used. The outcome assessor will be blinded. The outcome assessor will not know whether participants are from aerobic training, biofeedback training or placebo group. Single blinding will be used in this study because the results are less likely to be biased.

### Eligibility screening questionnaire

The Migraine screen questionnaire (MS-Q) is a five-item migraine screening questionnaire developed for use in clinical practice. The questionnaire is based on the international headache society criteria (IHS) on migraine diagnosis [32]. Each of the five items is a structured questionnaire that has an option of yes/no. A score of 0 is assigned for each “NO” response and 1 for each “YES” response. The total score is 5, where a cut-off point of ≥4 was used to indicate a case of migraine [33].

Visual Aura Rating Scale (VARS) is the weighted sum of the presence of five visual symptom characteristics: duration 5–60 min (3 points), develops gradually ≤5 min (2 points), scotoma (2 points), zig-zag lines (2 points), and unilateral (1 point). The maximum score is 10 points. A VARS score of 5 or more diagnosed migraine with aura [34]. The newly validated instrument to assess COVID-19 among migraine participants will also be used to exclude the other secondary headache.

Additionally, the International Classification of Headache Disorders 3^rd^ edition (ICHD-3) criteria will be evaluated, and it suggests at least five of seven attacks fulfilling the criteria. [35]. Migraine may be diagnosed without aura with the following diagnostic criteria:

5+ attacks fulfilling the other criteriaHeadache attacks that last from 4 to 72 hours (untreated or unsuccessfully treated)Headache consisting of at least 2 of the following characteristics: unilateral location, pulsating quality, moderate/severe pain intensity, and aggravation by or causing avoidance of routine physical activity (i.e., walking or climbing stairs)During the headache, the presence of at least one of the following: nausea/vomiting, photophobia/phonophobiaNot better accounted for with another ICHD-3 diagnosis

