### Inclusion and exclusion criteria

The target participants for this research will be undergraduate and postgraduate students from Universiti Tunku Abdul Rahman. The participants who fulfil the following criteria will be recruited for the interventional phase. 4 of 5 on the Migraine Screen Questionnaire, and 5 of 7 on International Classification of Headache Disorders 3rd edition (ICHD-3). Both genders aged between 18–40 years. The participants with a score of more than or equal to 5 on the visual aura rating scale, diagnosed to have a secondary headache (headache attributed to the causative disorder example: infection, trauma, or injury to head/ or neck) [28], pregnancy, took medication for neurological conditions like stroke, multiple sclerosis and took medications for cardiorespiratory conditions like asthma, took medications for headache and unwilling to participate will be excluded.

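### The visual aura item used for exclusion credits gradual development only up to 5 minutes, so slowly spreading symptoms lose 2 points and some people with aura could be enrolled

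*Protocol article*

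**What the plan says.** The article's section on the eligibility screening questionnaire defines VARS as a weighted sum of five visual features:

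- Duration: "duration 5–60 min (3 points".
- Development: "develops gradually ≤5 min (2 points".
- The remaining three: "scotoma (2 points), zig-zag lines (2 points), and unilateral (1 point".

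It adds "The maximum score is 10 points" and sets the decision rule: "A VARS score of 5 or more diagnosed migraine with aura". The section on inclusion and exclusion criteria, like the abstract, then excludes anyone with "a score of more than or equal to 5 on the visual aura rating scale". The headache criteria listed in the screening section are those for migraine without aura, so the intended population is clear. The development item appears nowhere else with a different limit.

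**The concern.** A feature meant to recognise slow development needs a lower time limit. The printed item has only an upper one. Within the range that scores, faster is always acceptable. Beyond 5 minutes, the slower and more clearly gradual the development, the more certainly the points are lost. Label and limit pull in opposite directions.

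This matters because the item feeds a hard exclusion threshold. Its 2 points can move a volunteer across the cut-off of 5, and the error would admit people whom the exclusion is meant to keep out. VARS is the only scored aura screen that the article describes. Allocation uses the MIDAS disability level, and the confounders listed under Outcomes do not include aura, so no later step named in the article would identify such people.

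**Working it through.** **Inputs** (all from the screening section): duration 3, development 2, scotoma 2, zig-zag lines 2, unilateral 1; cut-off 5.

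**The plan's own figure.** 3 + 2 + 2 + 2 + 1 = 10, which matches the stated maximum. The weights are consistent, and only the development limit is in question.

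**Where the item decides.** Let S be the sum of the other four items. The development item alone settles exclusion when S < 5 and S + 2 ≥ 5, that is, when S is 3 or 4. The four items have 2⁴ = 16 yes/no patterns, and five meet this condition:

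| Other features present | S | S + 2 |
|---|---|---|
| Duration only | 3 | 5 |
| Duration + unilateral | 4 | 6 |
| Scotoma + unilateral | 3 | 5 |
| Zig-zag + unilateral | 3 | 5 |
| Scotoma + zig-zag | 4 | 6 |

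**Which of these can admit slowly developing aura.**

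- The last three rows lack the duration points, so the symptom lasts less than 5 or more than 60 minutes. A symptom shorter than 5 minutes cannot develop over more than 5 minutes. Wrongful admission in these rows therefore needs a symptom longer than 60 minutes.
- With a duration of 5–60 minutes, adding scotoma or zig-zag lines gives at least 3 + 2 = 5. That person is excluded whatever the development item scores.
- This leaves the first two rows for a symptom of 5–60 minutes. Example: a unilateral symptom lasting 20 minutes and developing over 10 minutes scores 3 + 1 + 0 = 4 as printed and is enrolled. With credit for gradual development it scores 3 + 1 + 2 = 6 and is excluded.

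**The opposite error.** If the assessor applies only the time limit, an abrupt 20-minute symptom with no other feature scores 3 + 2 = 5 and is excluded; without the credit it scores 3 and is kept. Scotoma plus zig-zag lines lasting 1 minute would score 2 + 2 + 2 = 6, against 4 without the credit. If the assessor also requires the word gradually, neither case arises.

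**Effect of reversing the sign.** Weights, maximum and cut-off stay the same. Only who earns the 2 points changes, and development in exactly 5 minutes satisfies either version.

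**The case against.** The strongest reply is that the item has two conditions, gradual and within 5 minutes. A reader might infer from the bare limit that the scale rewards abrupt onset. The text does not support that as a general statement: a symptom that appears at once does not develop gradually, and an assessor who applies the whole phrase would give it no points. This part of the objection stands. It does not rescue the item, because under the same reading a symptom that spreads over 10 minutes still loses the points.

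Second, a journal article is summarising a cited instrument. The sign may be reversed only in print while the site form is correct. That is possible, and the form is not shown, so actual misclassification cannot be asserted. A text-extraction fault is less likely, since the same section prints the opposite sign correctly for the migraine screen cut-off of ≥4.

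Third, a reader might take five of 16 as a rate of misclassification. It counts patterns, not people, and for the ordinary 5–60 minute symptom only two patterns matter.

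Fourth, a reader might argue that admitted aura cases would inflate the variance of the EEG primary endpoint. The article says nothing on how aura affects that endpoint, so the claim has no support here. Screening also precedes random allocation, so any misclassification does not favour an arm.

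Finally, the listed headache criteria require that no other headache diagnosis explains the symptoms better. This is a partial second check, but it does not repair the stated VARS rule.

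**Conclusion.** The point holds as an internal contradiction in a stated eligibility rule. Applied as printed, the item withholds 2 points from visual symptoms that develop over more than 5 minutes. It would enrol some volunteers whom the exclusion is meant to remove: for symptoms of 5–60 minutes, those with duration alone or duration plus unilateral. Wrongful exclusion of abrupt symptoms is a further possibility only where the word gradually is disregarded.

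The conclusion on enrolment assumes that screening follows the printed wording, which the article does not show. How many people this would touch cannot be estimated from what is given. The consequence is a study population that departs from the without-aura group intended. Type I error, power and the validity of the randomised comparison are not at issue. The correction should be made because the item is part of a decision threshold and costs almost nothing to put right.

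**What to change.** Compare the printed item with the cited scale and with the form used at screening, then correct the article and, if needed, the form so that label and limit agree. The internal logic points to 5 minutes or more, but the cited source, which is not at hand here, must confirm it.

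If the form is already right, a correction to the published text is enough. If it carried the printed version, re-check every screened volunteer, enrolled or rejected, whose other four items sum to 3 or 4. Filed answers suffice only where the development time itself was recorded. A bare no to the printed item cannot separate abrupt from slow development, so those volunteers would need to be asked again.

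The cost is one changed sign, a check of the form and, in the worse case, a short follow-up question to the borderline volunteers.
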